## Abstract

**Introduction:**

Non-specific low back pain (NSLBP) is a prevalent condition affecting individuals worldwide, leading to significant disability and healthcare costs. Traditional treatment methods have shown limited efficacy, prompting the exploration of innovative approaches. Core stability exercise (CSE) has emerged as a promising rehabilitation strategy, yet optimal activation of local muscle systems remains to be fully understood. This trial aims to assess the efficacy of superimposing neuromuscular electrical stimulation (NMES) onto CSE for improving muscle activation, function, and proprioception in NSLBP patients.

**Methods and analysis:**

A total of 52 participants aged 18–60 years with NSLBP will be randomly allocated into two groups: (1) experimental group receiving NMES superimposed on CSE and (2) control group undergoing the same CSE with sham NMES. Interventions will occur three times per week for six weeks. The primary outcome measures will encompass surface electromyography (sEMG) to assess muscle activity and muscle activation timing. Secondary outcomes will include the evaluation of pain intensity using the Visual Analog Scale (VAS) and disability measured by the Oswestry Disability Index (ODI), as well as proprioception assessed through joint repositioning error (JRE) and muscle thickness evaluated via real-time ultrasound image (RUSI). Data will be collected at baseline, after six weeks, and at a six-month follow-up. A mixed ANOVA will be employed to compare differences among groups and to analyze trends over time as well as interaction effects between treatment and time.

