### Sample size calculation

The sample size for this study is determined based on previous findings reported by Songjaroen et al [17]. The test statistic used to calculate the sample size was based on a mixed ANOVA. The calculation is based on the anticipated effect size for LM activation improvement, with a large effect size (Cohen’s dz = 0.7), a statistical power of 80%, a significance level of 5%, and a standard deviation of 0.05 points. Using G*Power 3.1 software for the analysis, it is calculated that at least 43 participants are required. Considering an anticipated dropout rate of 20%, a total of 52 participants will be recruited for the study (26 in the experimental group and 26 in the control group).

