### Primary outcome measures

Surface Electromyography (sEMG) Muscle Activity: Muscle activity will be recorded using the MegaWin ME6000-T8 surface electromyography system (Finland). The system will be set to manual recording mode, utilizing low-pass bipolar analog signals with a 32-bit microcomputer. The instrument sensitivity will be set to 1 µV, with a filtering range of 8–500 Hz and a sampling frequency of 1000 Hz. The measurements will be conducted using a differential preamplifier and a free raw data measurement method. Standardized disposable electrodes will be used to eliminate the possibility of reuse. The connection of the electrodes to the electromyography device will be adjusted to ensure that it does not impede the participants’ movements and to prevent the disconnection of the surface electrodes or data line connectors due to tension. The electrode spacing will be set to 2.5 cm and positioned parallel to the muscle fibers of the following muscles: external oblique(EO) (approximately 15 cm lateral to the umbilicus), TrA/IO (2 cm superior and medial to the anterior superior iliac spine), erector spinae(ES) (2 cm lateral to the spinous processes of L1), LM (2 cm lateral to the spinous processes of L5), and anterior deltoid (two fingerbreadths from the anterior aspect of the acromion) [24]. All electrodes will be placed on the more severely affected side of NSLBP patients. The reference electrode will be connected to the iliac crest. The EMG data will be measured for 5 seconds. After excluding the first and last second, the root mean square (RMS) values of the 3 seconds of sEMG signal will be calculated [25].

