Measurement of Muscle Activation Timing: To assess the latency of trunk muscle activation, participants will perform a lifting task while standing quietly, which introduces an inherent perturbation to the trunk and requires anticipatory postural adjustments (APA) [24]. The electrode placements will be the same as those used for muscle activity monitoring. Participants will stand with their elbows fully extended at 0°, shoulders flexed at 40°, and grasp the handles of a 5 kg box placed on a table in front of them. They will be instructed to lift the box to a shoulder flexion angle of 90° as quickly as possible and maintain this position for 3 seconds. After familiarizing themselves with the movement, participants will complete three repetitions of the lifting task, with a 1-minute interval between each trial. If any trunk or pelvic motion is observed during the trial, that attempt will be considered a failure. For sEMG processing, the procedures for manually selecting activation timings are as follows: Raw sEMG signals will first be filtered using a band-pass filter (20–450 Hz) to remove noise and artifacts. The baseline sEMG levels will be defined by calculating the RMS value of a 500 ms resting period before the onset of muscle activation. Muscle activation will be identified when the sEMG signal exceeds 3 standard deviations (SD) above the baseline RMS for a minimum duration of 50 ms. If necessary, trained assessors will visually inspect and manually adjust the activation timing to account for signal variations and artifacts, ensuring consistency across trials. The relative difference in onset activation times between each trunk muscle and the anterior deltoid will be calculated using the following formula: Relative Onset Activation Time Difference = Onset Activation Time of Trunk Muscle - Onset Activation Time of Anterior Deltoid (ms) [26]. A positive value indicates that the target trunk muscle is activated after the anterior deltoid. The average onset time from the three repetitions for each trunk muscle will be computed and used as the basis for data analysis.

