Proprioception Testing: Proprioception will be assessed using joint repositioning error(JRE) as the primary outcome measure. Participants will be seated with their feet flat on the ground and hands resting on their thighs. The examiner will guide the participant into the neutral position of the lumbar spine. The measurement will start at the sacral level 1 (S1), with the center of a 10 cm measuring tape positioned at the measurement starting point. A laser pointer will be placed 50 cm behind the participant, aimed at the center of the 10 cm measuring tape located at S1. The examiner will instruct the participant to remember the target position, then perform two maximum anterior pelvic tilts and posterior pelvic tilts, holding each position for 5 seconds before returning to the neutral target position. The deviation from the starting point will be measured in centimeters as the JRE [29]. Prior to the assessment, participants will undergo two practice trials to familiarize themselves with the testing procedure. A total of three tests will be conducted, with a 1-minute rest between each test. The average of the absolute errors from the three measurements will be calculated to represent the magnitude of the error.

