### Statistical analysis

Statistical analyses will be performed using SPSS Version 22.0 software (IBM). Continuous variables that conform to a normal distribution will be expressed as means ± standard deviations, while non-normally distributed continuous variables will be presented as medians (interquartile range). Categorical variables will be reported as proportions and rates. Baseline comparisons for continuous variables will be conducted using t-tests or non-parametric tests as appropriate, while baseline comparisons for categorical variables will utilize chi-square tests. For measurements taken at multiple time points, a mixed ANOVA will be employed to compare differences among groups and to analyze trends over time as well as interaction effects between treatment and time. In the presence of significant interaction effects between time and group, post hoc tests will be conducted with Bonferroni adjustments for multiple comparisons. The significance level will be set at 0.05 (two-tailed).

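### Eight unranked primary sEMG variables are each tested at two-sided 0.05, and the stated Bonferroni rule does not control error across them

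*Protocol article*

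**What the plan says.** - **Primary outcome.** Abstract, Methods and analysis: "The primary outcome measures will encompass surface electromyography (sEMG) to assess muscle activity and muscle activation timing". The Primary outcome measures section describes both measures and gives neither precedence.
- **Muscles.** The same section places electrodes on "external oblique(EO) (approximately 15 cm lateral to the umbilicus), TrA/IO", then on ES, and on "LM (2 cm lateral to the spinous processes of L5), and anterior deltoid". The deltoid serves as the time reference for onset. One side is recorded: "All electrodes will be placed on the more severely affected side of NSLBP patients".
- **Timing.** Onset is analysed muscle by muscle: "The average onset time from the three repetitions for each trunk muscle will be computed and used as the basis for data analysis".
- **Analysis.** The Statistical analysis section applies a mixed ANOVA to outcomes measured at several times (baseline, week 6, six months), with a two-tailed level of 0.05. On multiplicity it says: "In the presence of significant interaction effects between time and group, post hoc tests will be conducted with Bonferroni adjustments for multiple comparisons".
- **Sample size.** "The calculation is based on the anticipated effect size for LM activation improvement". No measurement method and no time point is attached to that phrase.
- **A stray label.** Under Secondary outcome measures: "Proprioception will be assessed using joint repositioning error(JRE) as the primary outcome measure".

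**The concern.** A trial that claims success at the 5% level needs either one test that decides it or a rule that holds the error at 5% over all the tests that may decide it. This protocol names a family of primary variables and gives a multiplicity rule, but the rule works inside each ANOVA and not between them. As written, a significant interaction in one of the eight variables could be reported as meeting the primary outcome, whichever muscle or measure produced it. The stated 0.05 would then describe each test, not the primary claim. It also matters that at most one of the eight variables has a stated basis for its power.

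**Working it through.** The protocol states no family-wise error rate, so there is no figure of its own to reproduce.

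**Inputs from the protocol**
- Primary measures: 2 (RMS activity, onset-time difference).
- Trunk muscles: 4 (EO, TrA/IO, ES, LM), on one side.
- Level: 0.05 two-sided.
- Arm size: 26.
- Times: 3, handled within one mixed ANOVA per variable.

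**Step 1: the number of primary tests.** 2 measures × 4 muscles = 8 variables, hence 8 group × time interaction tests. The two follow-ups add no further tests at 0.05, because they sit inside each ANOVA.

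**Step 2: independent tests.** Family-wise error = 1 − (1 − 0.05)^8 = 1 − 0.6634 = 0.337, about 34%.

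**Step 3: correlated tests.** Variables from the same person are likely to be positively correlated. The protocol gives no value, so a range is assumed. Simulating eight two-sided normal tests with a common correlation gives:

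| Assumed correlation | 0 | 0.3 | 0.5 | 0.7 | 0.8 |
|---|---|---|---|---|---|
| Family-wise error | 33.8% | 30.2% | 25.0% | 19.0% | 15.7% |

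**Step 4: the planned test, under three success rules.** The interaction F test was simulated under the null with 26 per arm, three times, an assumed within-person correlation of 0.5 and 4,000 runs. Follow-up values were not baseline-adjusted.

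| Success in any of 8 variables means | corr. 0 | 0.3 | 0.5 | 0.8 |
|---|---|---|---|---|
| interaction significant | 33% | 31% | 26% | 17% |
| interaction significant and a Bonferroni-significant arm difference at a follow-up | 7.2% | 7.0% | 6.8% | 4.5% |
| interaction or group main effect significant | 56% | 52% | 45% | 30% |

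The first row agrees with Steps 2 and 3. The spread between rows shows how much depends on a success rule that the protocol does not state.

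**Step 5: what control would cost.** With all eight kept primary, the strictest level (Bonferroni, or the first Holm step) is 0.05/8 = 0.00625. The sample-size section gives an effect of 0.7, labelled dz; reading it as a between-arm standardised difference is an assumption. On that reading, 26 per arm gives about 70% power at 0.05, 59% at 0.025 (two tests) and 38% at 0.00625. For 80% power the arm sizes are 33, 39 and 53.

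**The case against.** **The detail may sit in an analysis plan.** The article is a condensed document, and a cross-variable procedure could be set out elsewhere. This limits the point but does not remove it. Which outcome is primary is protocol content, and the article itself declares the family, sets the level and states a multiplicity rule that does not cover that family.

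**The plan does adjust.** This is partly right. Time-specific comparisons are gated by the interaction and carry Bonferroni. A reader might count two measures, four muscles and two follow-ups as 16 tests at 0.05 and arrive at 1 − 0.95^16 = 56%. The Statistical analysis section does not support that count.

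**34% is a ceiling for the interaction tests.** This stands. Positive correlation lowers it. A reader might add that the rate could be higher, and it could if a group main effect also counted as success. The ANOVA is indeed meant to compare groups as well, but nothing says that a main effect would meet the primary outcome. In the other direction, a rule requiring both the interaction and an adjusted arm difference would bring the rate to about 5–7%. The protocol does not adopt that rule either, and does not say whether its post hoc tests compare arms or times.

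**The sample size already identifies the primary.** A reader might infer that the trial is sized on LM sEMG RMS. The text says only LM activation, and the Secondary outcome measures section defines an ultrasound activation ratio and measures LM thickness. Either could be meant.

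**JRE as a further primary.** A reader might infer this from the stray label. The abstract and the section heading both place JRE among the secondary outcomes, so the sentence most naturally means the main measure of proprioception.

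**Conclusion.** The concern holds in this form: eight primary variables, no order among them, each tested at two-sided 0.05, and no stated control across them. If any one significant interaction counts as success, the family-wise error is up to about 34% under independence and roughly 16–30% at common correlations of 0.8 to 0.3. These figures rest on two assumptions that the protocol does not settle: the success rule and the correlation. The count of eight takes each trunk muscle as its own variable. The text says this outright for timing; for activity it follows from the electrode list, in which no muscle is singled out. The JRE wording is a minor clean-up and adds nothing to the error rate.

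**What to change.** Before unblinding, in the protocol and the registry entry:

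1. Name one primary variable and one time contrast. LM activation is the natural choice because the sample size refers to it. The sponsor should first confirm whether that means sEMG RMS or the ultrasound ratio, and should state the time contrast, which the sample-size section leaves open.
2. Make the other muscles, the timing variables and the other contrasts secondary or exploratory.
3. If several variables must stay primary, list them and apply Holm across their group × time tests.
4. Reword the JRE sentence so that it calls JRE the main measure of proprioception.

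The cost is wording and a registry update. Under items 1 and 2, fewer variables can carry a confirmatory claim. Under item 3, power per variable falls (see Step 5 of the check), so a short list is much cheaper than all eight.

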**Trial registration:**

**Trial registration number:** Chinese Clinical Trial Registry (ChiCTR2400092409)

## Introduction

Low back pain (LBP) is one of the most common global health issues, contributing to significant disability, societal burden, and healthcare costs. It is estimated that 75%–85% of individuals will experience at least one episode of LBP during their lifetime, a trend that has steadily increased over the past two decades [1]. As of 2017, the global prevalence of LBP was approximately 7.5%, equating to approximately 577 million individuals worldwide [2]. After excluding specific pathologies affecting the lumbar spine, about 90% of LBP cases cannot be attributed to a specific diagnosis and are thus classified as non-specific low back pain (NSLBP) [3]. Given the high prevalence and impact of NSLBP, it is crucial to develop and refine treatment strategies that can effectively improve patient outcomes.

One such approach is core stability exercise (CSE), which has emerged as a common intervention for LBP. CSE focuses on strengthening the muscles of the trunk and pelvis, enhancing movement patterns in the transverse and frontal planes. This approach not only prevents and reduces pain and disability but also improves spinal stability and flexibility, ultimately promoting the restoration of normal motor patterns [4]. However, despite its advantages, the long-term effects of CSE on pain relief and functional improvements remain limited. Issues such as poor patient adherence, time-consuming training sessions, and insufficient long-term effects persist [5].

A key challenge in treating NSLBP lies in addressing abnormal trunk muscle activation patterns. Patients with NSLBP exhibit abnormal activation of the trunk muscles, including insufficient and delayed activation, especially in the deep trunk muscles such as the transversus abdominis(TrA) and lumbar multifidus(LM) [6]. This dysfunction in deep muscle activation contributes to impaired spinal stability and movement patterns, which can exacerbate pain and disability. Conventional CSE, particularly in unloaded forms, may not adequately address these issues due to difficulties in effectively engaging these deep muscles through voluntary effort alone [7].

Neuromuscular electrical stimulation (NMES) offers a potential solution by directly stimulating the paraspinal muscles to enhance muscle contraction and motor unit recruitment. NMES, when combined with voluntary movements in exercise training, can further activate spinal reflex pathways and enhance central descending drive, improving muscle function and proprioception. This dual approach increases synaptic efficiency of somatosensory pathways and alters cortical activity in both primary and secondary somatosensory cortices, contributing to more effective motor control and muscle recruitment [8,9]. Studies have shown that NMES superimposed on exercise training demonstrates significant positive effects on improving exercise performance and reducing time expenditure compared to using NMES alone or engaging in voluntary exercise training alone, while also providing additional neurological and physiological benefits [10,11].

Despite these promising findings, there is limited research on the effects of NMES superimposed on CSE in patients with NSLBP, and high-quality clinical randomized controlled trials are lacking. Furthermore, existing studies often do not address the complex interplay of motor control, proprioception, and cortical changes induced by this combined intervention. Therefore, the primary aim of this study is to investigate the efficacy of NMES superimposed on CSE in improving core muscle activation, proprioception, and spinal stability in NSLBP patients. We hypothesize that, compared to a standard CSE alone, the NMES-combined intervention group will induce greater core muscle activation, more effectively enhance trunk stability, reduce pain, and improve function.

## Methods

### Study design

This study will be a single-center, prospective, randomized, sham-controlled trial conducted at the outpatient rehabilitation center of the Sir Run Run Shaw Hospital, affiliated with Zhejiang University School of Medicine. A total of 52 participants will be recruited and randomly assigned in a 1:1 ratio to one of the following two groups: (a) experimental group, receiving NMES superimposed on CSE to enhance activity levels; (b) control group, receiving the same CSE with sham NMES. All participants in both groups will undergo 20-minute sessions, three times per week, for a 6-week intervention period. The study outcomes will be evaluated before (t0), six weeks after initiating interventions(t1), and six months (t2) after starting the protocol. The study protocol follows the standards described in the “Standard Protocol Items: Recommendations for Interventional Trials” guideline (S1 File) [12].

### Approval and registration of the study

The study design and procedures have been approved by the Institutional Review Ethics Committee of Sir Run Run Shaw Hospital, affiliated with Zhejiang University School of Medicine (Approval No. 2024–0285 and Date of review: April 25, 2024). The trial has also been prospectively registered with the Chinese Clinical Trial Registry (Registration No ChiCTR2400092409.) (S2 and S3 Files). We confirm that all methods will be conducted in accordance with the ethical standards of the Declaration of Helsinki. Participants will be informed about the study’s purpose and procedures, and those meeting the inclusion criteria will be asked to sign a detailed consent form (S4 File).

### Participant involvement

None of the participants will be involved in the design, implementation, or dissemination plans of this study. Patients who meet the inclusion criteria will be recruited for the randomized controlled trial (RCT) through our outpatient department, posters, and social media platforms (from January 1st, 2025 to December 31th, 2026). Participants’ personal data, such as names, ages, and weights, will be stored in a coded digital format within a secure database, accessible only to the research personnel responsible for randomization and blinding. Upon completion of the trial, participants will have access to their individual study results.

### Eligibility criteria

Inclusion Criteria: (a)Participants aged between 18 and 60 years [13]. (b)History of LBP for at least 3 months, without radiculopathy, specific spinal disorders, or radicular pain [14]. (c)Visual Analog Scale (VAS) score≤6. (d)No received CSE or NMSE therapy within the past month. (e)Infrequent use of analgesics (less than 4 days per week). (f)No medication or medical conditions affecting muscle metabolism (e.g., corticosteroids). (g)Normal hearing and psychological status, with high adherence to participation. (h)All participants must sign the informed consent form. Exclusion Criteria are Pregnant or breastfeeding women [15]; Presence of severe underlying diseases such as cardiovascular, liver, or renal disorders; Participants with comorbid conditions like osteoarthritis, gout, tumors, acute trauma, or fractures that affect daily living capabilities [16]; History of spinal surgery; Contraindications for NMES (e.g., pacemakers, edema, sensory abnormalities, thromboembolism); Participants currently enrolled in other clinical trials for interventions targeting NSLBP.

### Sample size calculation

The sample size for this study is determined based on previous findings reported by Songjaroen et al [17]. The test statistic used to calculate the sample size was based on a mixed ANOVA. The calculation is based on the anticipated effect size for LM activation improvement, with a large effect size (Cohen’s dz = 0.7), a statistical power of 80%, a significance level of 5%, and a standard deviation of 0.05 points. Using G*Power 3.1 software for the analysis, it is calculated that at least 43 participants are required. Considering an anticipated dropout rate of 20%, a total of 52 participants will be recruited for the study (26 in the experimental group and 26 in the control group).

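### The sample size rests on a paired effect size (dz = 0.7) that is not an input to the two-arm mixed ANOVA it names, so the stated 80% power is not supported

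*Protocol article*

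**What the plan says.** All sizing statements are in the protocol article, Sample size calculation. On the test: "The test statistic used to calculate the sample size was based on a mixed ANOVA". On the target: "The calculation is based on the anticipated effect size for LM activation improvement". The remaining inputs are "dz = 0.7), a statistical power of 80%, a significance level of 5%, and a standard deviation of 0.05 points". The result is that "it is calculated that at least 43 participants are required", raised to 52 (26 per arm) for an expected 20% dropout.

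Elsewhere, Study design describes two independent groups allocated 1:1 and assessed at three times. Statistical analysis plans a mixed ANOVA with group, time and interaction effects, and adds: "The significance level will be set at 0.05 (two-tailed)". Under Primary outcome measures, muscle activity is an amplitude ("the root mean square (RMS) values of the 3 seconds of sEMG signal will be calculated") and activation timing is an onset difference in milliseconds.

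**The concern.** Three things do not fit together.

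- **Effect-size index.** dz belongs to a paired comparison, but the trial's question is a difference between independent arms. The text does not say whether 0.7 is a change within a group or a difference between groups.
- **Inputs and test.** A mixed-ANOVA calculation works from f, the term tested, the number of measurements and, for some options, their correlation. Apart from the three visits, none of these is given. The two figures that are given (dz and an SD) are not used by it.
- **Units.** Points are not the unit of either primary outcome as defined. The target, LM activation, is not tied to a named outcome: the secondary outcomes also define an ultrasound activation ratio.

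The 80% figure is the only justification for the trial's size. If it is too high for the effect the trial hopes to find, a null result will be read as stronger evidence of no benefit than it is.

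**Working it through.** **Inputs.** From Sample size calculation: 0.7, 80% power, 5% significance, 43 required, 20% dropout, 52 recruited. From Statistical analysis: two-sided. From Study design: two arms, 1:1, m = 3 visits. My assumptions: equal correlation ρ between visits, and a between-arm difference that is absent at baseline and equal at both follow-ups.

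**1. Trying to reproduce 43 from the printed inputs.**
- Paired t-test, noncentrality 0.7√n: power is 79.9% at n = 18 and 82.3% at n = 19, so 19 are needed.
- Two-sample t-test, noncentrality 0.7√(n/2) with n per arm: power is 79.97% at 33 and 81.2% at 34, so 34 per arm, 68 in all.

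Neither gives 43.

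**2. Reproducing 43 with added choices.** Convert 0.7 to f = 0.7/2 = 0.35, test the group-by-time interaction and use G*Power's 'as in SPSS' option: λ = f²(N − 2)(m − 1), with 2 and 2(N − 2) degrees of freedom.
- N = 42: power 79.1%.
- N = 43: λ = 0.1225 × 41 × 2 = 10.05, power 80.2%.
- N = 52: power 88.0%.

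So 43 is exactly the minimum on this route. Other unstated choices give other answers at f = 0.35: 41 under the Cohen option, 15 under the default interaction option with ρ = 0.5, and 45 or 43 for the between-groups term with ρ = 0.5 or 0.45.

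**3. What λ = 10.05 means as a treatment effect.** Under the assumed pattern the interaction noncentrality is λ = N·d²/3, where d is the between-arm difference in change divided by the SD of change. Setting 43·d²/3 = 10.05 gives d = √(3 × 10.05/43) = 0.84. The route that yields 43 is therefore powered for 0.84 change-score SDs, not 0.7. The rule f = d/2 is for a simple difference between two group means and does not carry over to this interaction f.

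**4. Power if 0.7 is a between-arm difference.**
- *Unadjusted two-sample t-test:* 61.0% at 43 (22/21), 69.7% at 52 (26/26), 60.0% at 42 (21/21), 58.9% at 41 (21/20).
- *Interaction, 0.7 in change-score SDs:* at 43, λ = 43 × 0.49/3 = 7.02, power 64%. At 52, λ = 8.49, power 73%.
- *Interaction, 0.7 in raw-score SDs:* the change-score effect is 0.7/√(2(1 − ρ)), so λ = N × 0.49/(6(1 − ρ)).

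| ρ | N = 42 | N = 43 | N = 52 |
|---|---|---|---|
| 0.3 | 48% | 49% | 58% |
| 0.5 | 63% | 64% | 73% |
| 0.6 | 73% | 74% | 83% |
| 0.7 | 85% | 86% | 92% |

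**5. Dropout.** 43 × 1.2 = 51.6, which rounds to the stated 52. Allowing for 20% loss means dividing: 43/0.8 = 53.75, so 54. Conversely, 52 × 0.8 = 41.6, so about 41 to 42 evaluable, below the stated minimum of 43.

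**The case against.** The strongest reply is that the protocol names a mixed ANOVA, and a mixed ANOVA does return 43 (step 2). The t-test figures replace the stated test with another and read dz as a between-group d, which the text never says. The options chosen, the correlation and the tested term may also sit in a fuller document that is not shown.

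Much of this stands. A reader might infer that power is simply 61%, or 70% with all 52, and that 80% has been shown to be missed. The documents do not support that. They do not fix 0.7 as a between-arm effect, the planned test is not a t-test, and 70% assumes no dropout although 52 already contains the dropout allowance. With a high enough correlation, power exceeds 80%. Nor does the odd total of 43 count against the calculation, since repeated-measures F tests in G*Power return a total N.

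The reply does not rescue the 80% claim. Finding a set of options that hits 43 does not show that they were used, and that set corresponds to an effect of 0.84, not 0.7. Nor is this just detail left out for brevity: the section prints inputs that do not belong to the test it names. The unit of the SD is a lesser matter. A standardised effect makes the SD redundant, so it does not alter N, but it leaves unclear which variable was sized.

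**Conclusion.** The point holds as a mismatch between inputs and design, and as an unsupported power claim; a proven shortfall is not established. The printed inputs give 19 or 68, not 43. The recovered 43 depends on unstated choices and on a larger effect than 0.7.

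For a between-arm 0.7, the planned interaction test at 43 has 64% power if 0.7 is in change-score SDs. In raw-score SDs it has 49% to 86% for correlations of 0.3 to 0.7. Among the correlations tabulated, only 0.7 reaches 80% at 42 or 43, and the protocol states no correlation. These figures rest on equal correlations and an equal effect at both follow-ups.

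Separately, and without any such assumption, the dropout step leaves about 41 to 42 evaluable against the 43 called for.

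**What to change.** Keep 52 and rewrite the sample size section.

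- Name the LM sEMG outcome that was sized. Give the between-arm difference and SD in its own units, in place of dz and the SD in points.
- State whether the effect is standardised by the raw-score or the change-score SD.
- State the term tested, the f used and how it was obtained, the G*Power option, and the assumed correlation with its basis.
- Report the power that 52 recruited, about 41 to 42 evaluable, gives over a stated range of correlations. If 0.7 in raw-score SDs is kept, the N = 42 column above shows the form this would take.
- Correct the dropout statement: 20% loss from 52 leaves about 41 to 42, and retaining 43 would take 54.

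The cost is wording in one section. The stated power may become less favourable. No participants are added.

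### Recruiting 52 does not cover the anticipated 20% dropout: 41 to 42 completers are expected, against the protocol's own minimum of 43 (minor correction)

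*Protocol article*

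**What the plan says.** The protocol article's Sample size calculation section gives three linked figures.

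- **Minimum:** "it is calculated that at least 43 participants are required".
- **Dropout and total:** "Considering an anticipated dropout rate of 20%, a total of 52 participants will be recruited for the study".
- **Split:** "26 in the experimental group and 26 in the control group".

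The Study design section repeats the total and fixes the allocation: "A total of 52 participants will be recruited and randomly assigned in a 1:1 ratio". The Abstract also gives 52. The minimum is tied to "a statistical power of 80%, a significance level of 5%, and a standard deviation of 0.05 points", and the Statistical analysis section sets the test as two-tailed.

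The article does not print the formula that leads from 43 to 52. It gives no second dropout rate, no rule for replacing participants who leave, and no other allowance that would make up a difference.

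**The concern.** A dropout rate is a share of the people recruited. To end with a required number after losses, that number is divided by one minus the rate. Multiplying it by one plus the rate gives a smaller total, which falls short when the anticipated losses occur. The stated 52 is what the multiplication gives.

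What is at stake is whether the recruitment target does what the protocol says it does. The 52 is presented as enough to keep 43 after 20% dropout. If it is not, the nominal 80% power is missed at the dropout rate the protocol itself anticipates, and the justification of a figure given in three places in the article is incorrect.

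**Working it through.** **Inputs**, all from the Sample size calculation section unless noted:

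- required minimum: 43
- anticipated dropout: 20%
- recruited total: 52, as 26 + 26
- allocation: 1:1 (Study design)
- power and significance level: 80% and 5%, two-tailed (sidedness from Statistical analysis)

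**Step 1. Reproduce the stated total.**
Required × (1 + dropout) = 43 × 1.20 = 51.6, rounded up to 52. This matches the protocol. The match makes this the likely route, but it remains an inference.

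**Step 2. Expected completers with 52 recruited.**
Recruited × (1 − dropout) = 52 × 0.80 = 41.6, that is 41 to 42. Per arm: 26 × 0.80 = 20.8. The minimum is 43, so the expected shortfall is 43 − 41.6 = 1.4 participants. This step does not depend on how 52 was reached.

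**Step 3. Dropout that 52 can absorb.**
52 − 43 = 9 losses, and 9/52 = 17.3%, compared with the stated 20%.

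**Step 4. Totals that do meet 43 at 20%.**
- Required / (1 − dropout) = 43 / 0.80 = 53.75, rounded up to 54 (27 per arm). Check: 54 × 0.80 = 43.2.
- If the odd number 43 is first rounded up to equal arms of 22: 22 / 0.80 = 27.5, rounded up to 28 per arm, or 56 in total. Check: 56 × 0.80 = 44.8.

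**Step 5. Effect on power.**
Accept the protocol's claim that 43 gives 80% power. By a normal approximation, power at n completers is Φ[(1.960 + 0.842) × √(n/43) − 1.960].

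| Completers | Approximate power |
|---|---|
| 43 | 80% (by assumption) |
| 42 | 79.1% |
| 41.6 | 78.7% |
| 41 | 78.1% |

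The loss is between 1 and 2 percentage points.

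**The case against.** The strongest objection concerns importance, not arithmetic. The expected gap is 1.4 completers, power falls by less than 2 points, and the gap appears only if dropout exceeds 17.3%. An anticipated dropout rate is a planning guess, and the difference between 17.3% and 20% lies well within the uncertainty of such a guess. This stands, and it is why the point is minor.

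A second objection is that the article says 43 participants are required without calling them completers. Reading 43 as the number left after losses is an interpretation, but the only natural one: an allowance for dropout is added so that the required number remains once people have left. A mixed ANOVA in its conventional form also uses participants measured at every time point.

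A third objection is that the 43 is itself unexplained. The section says "The test statistic used to calculate the sample size was based on a mixed ANOVA" and quotes "with a large effect size (Cohen’s dz = 0.7", which is an effect size for paired differences, without giving the correlation, the number of measurements or the effect tested. Simple readings of 0.7 give other totals: 19 for a two-sided paired t-test and 68 (34 per arm) for a two-sided two-sample t-test. None of the mixed ANOVA settings tried with f = 0.7 or 0.35 gave exactly 43. That uncertainty is larger than the difference between 52 and 54. It is a separate question, however. The present point takes 43 as given and shows only that 52 does not deliver it at 20% dropout.

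Three stronger readings are tempting, and the document supports none of them:

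- **That the trial is underpowered in any material way, or that its power claim collapses, because of this slip.** The figures show about 78% to 79% in place of 80%.
- **That the protocol demonstrably multiplied by 1.2.** No formula is printed, so it can only be said that it appears to have done so.
- **That 54 is the single correct total.** With 1:1 allocation and an odd minimum, 56 is equally defensible if rounding is done per arm first.

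**Conclusion.** The sentence is wrong as written, and the correction is minor. The minimum of 43, the dropout of 20% and the total of 52 cannot all hold, and rounding does not explain it, since 53.75 cannot round to 52. Nothing else in the article closes the gap.

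The size is 1 to 2 completers and 1 to 2 points of power. The shortfall rests on two assumptions: that 43 means participants remaining after dropout, and that 20% is a share of those recruited. The power figures assume further that 43 completers would give exactly 80%, which could not be confirmed from the inputs given, and they use a normal approximation. The trial's ability to answer its question is not changed by this point alone.

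**What to change.** Correct the one sentence in the Sample size calculation section. Keeping 52 is sufficient, with either of these statements:

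- 52 recruits preserve the required 43 at a dropout of up to about 17% (9 of 52); or
- at 20% dropout, 41 to 42 completers are expected, with power of about 78% to 79% on the assumption that 43 gives 80%.

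Either costs one sentence and no extra participants. If the authors prefer to keep both 43 and 20%, the consistent total is 54 (27 per arm), which is two more participants, or 56 (28 per arm), which is four more, if the minimum is first rounded up to 22 per arm. In that case the total must also be changed in the Abstract and the Study design section.
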